### Ethical aspects

The study was conducted in accordance with the Declaration of Helsinki and approved through the Research Ethics Committee from Hospital de Clínicas de Porto Alegre (HCPA) under number 2022–0634, CAAE 67679423.0.0000.5327. All participants will provide written informed consent before data collection.

Any changes to the protocol that could have an impact on the study’s conduction, including changes to the objectives, sample size, tools or that affect the participants in any way, will be communicated immediately to the Ethics Committee via email. Participants will be asked to read and sign the Informed Consent Form (ICF) when they enter the study. Participants will be given full details of the study’s characteristics and interventions. They will also be informed that they are free to withdraw from the study at any time. The Research Ethics Committee, which approved the study, demands periodical reports for the trial’s auditing. This process occurs with the investigators’ participation.

Adverse events will be monitored weekly by researchers ([name], [name], [name]) in each meeting through conversations with the participants. According to the type of adverse event, referral to the health care service of the sponsor institution will be made. The health care service of the sponsor institution will provide post-trial care and compensation to those who suffer harm for trial participation.

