### Recruitment

Recruitment will take place from March 4, 2024, to March 31, 2026, which is the estimated timeframe to achieve the calculated sample size. Participants will be recruited through posts on the researchers’ social networks, and those who express an interest will be contacted for an initial conversation via WhatsApp video call. This assessment will confirm the participant’s desire to participate in the study, the inclusion and exclusion criteria, and guidance on the study protocol. After confirming eligibility and signing the Informed Consent Form, the participants will be randomized and assigned to one of the two intervention groups: self-compassion or diet. The groups will take place weekly through face-to-face meetings, which will take place over eight weeks and will be one hour long. The group will be led by nutritionists previously trained in the two approaches. The adherence rate will be controlled, requiring a minimum participation of 75% (6 meetings) to be maintained in the entire study (baseline to eight weeks, three and six months follow-up).

Before the first meeting, all participants will answer an anamnesis and three validated scales for assessing eating behavior and body dissatisfaction, which will be available through the *Google Forms* platform. The same scales will be answered after the eight meetings (the end of the group), three months after the last meeting, and six months after the last meeting. Fig 2 shows the study flow diagram.

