### Data management

The data will be collected by two independent authors and stored in an SPSS® file database. The tools used to obtain the outcomes will be evaluated at the beginning (week 0) and after the intervention (week 8) and again at three and six months *follow-up*. All forms will be made available via *Google Forms.*

One of the researchers will send a WhatsApp message every week to promote participant retention and complete follow-up, encouraging participants to come to the meetings. Also, the messages sent will be the same for both groups and will include reminders about the meeting days, location, time, and any materials participants may need to bring for the activities. To those who discontinue or deviate from the intervention protocol, all data exclusion will be necessary.

The data collected will be saved on an institutional drive linked to the researcher in charge and shared only with the other researchers in the study. The data are expected to be stored for two and a half years (until the end of 2025), following the study schedule.

An interim analysis could be conducted if preliminary results need to be presented at scientific events relevant to the institutions involved in the study’s development. However, if such analyses could compromise the reliability of the data, they will not be performed*.* All authors could have access to interim results, but only the study coordinator ([name]) could decide to terminate the trial.

The plans for investigators and sponsor to communicate trial results are: a) Individual disclosure of the basal and post-intervention results to each participant; b) A public seminar with grouped results at sponsor institution to healthcare professionals; c) Public disclosure in scientific events, preprint, and scientific article publication.

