## Discussion

This study proposes a nutritional intervention protocol based on self-compassion techniques compared to a traditional approach with dieting, both for eight weeks, evaluating which has better results in body dissatisfaction and eating behavior in adult women with weight-related body dissatisfaction. Our hypothesis is that the intervention based on self-compassion techniques will be more effective in reducing body dissatisfaction and dysfunctional eating behavior in the participants.

Traditional weight loss programs, or restrictive diets, have been known and practiced for years [11,12]. These models encourage individuals to consciously restrict their diet and are effective in the short and medium term. However, studies indicate that the strategies generate emotional stress and develop dysfunctional behaviors in relation to food in the long term, compromising the individual’s physical and mental health [11,12,14]. In this sense, non-dietary interventions have shown important psychological benefits, such as improved well-being and decreased suffering, weight-related stigma, body dissatisfaction [19,20] greater eating competence [21] decreased cognitive restriction and lack of eating control [18]. For this reason, other approaches are needed to address body dissatisfaction issues and the relationship with food in adults.

To date, only observational studies have evaluated the relationship between self-compassion and body dissatisfaction and dysfunctional eating behavior. A study of 435 women, which aimed to relate self-compassion to the pressure for a thin body, indicated that self-compassion decreased the media pressure related to thinness, dysfunctional eating and the internalization of the thin ideal [41]. In women diagnosed with eating disorders who perceive themselves as disgusting and have an aversion to their bodies, self-compassion has also been shown to be positive [30]. More self-compassionate individuals seem to worry less about their bodies and weight and have more body appreciation [42], less body shame [31] and are less at risk of eating disorders and other harmful behaviors [43].

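### Adverse events are asked about only at the eight weekly meetings, so clinical harms after week 8, and harms in women who leave, are not systematically recorded

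*Protocol article*

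**What the plan says.** The Ethical aspects section of the protocol article gives a specific rule for adverse events. It fixes the frequency ("Adverse events will be monitored weekly by researchers") and the setting and method ("in each meeting through conversations with the participants"). The same section offers referral to the sponsor institution's health care service, and post-trial care and compensation for women harmed by taking part.

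The Recruitment section sets the length of the meetings ("which will take place over eight weeks and will be one hour long") and the later contacts. For the contact at the end of the group it says "The same scales will be answered after the eight meetings", and it repeats those scales "three months after the last meeting, and six months after the last meeting". The Data management section says "All forms will be made available via" Google Forms. The Discussion confirms that follow-up consists of questionnaires answered once the face-to-face meetings are over.

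Two rules concern women who leave. Recruitment requires attendance at 6 or more of the 8 meetings to be kept in the study, follow-up included. Data management states: "To those who discontinue or deviate from the intervention protocol, all data exclusion will be necessary".

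On expected harm, the Introduction describes energy-restricted programmes as harmful and says that such diets, combined with fear of weight gain and preoccupation with food, can be related to anxiety, depression and eating disorders. The Discussion adds that "studies indicate that the strategies generate emotional stress and develop dysfunctional behaviors in relation to food in the long term".

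**The concern.** Adverse-event enquiry is tied to attendance at a meeting. When the meetings stop, or a woman stops coming, the only described route for learning about harm stops too. The trial still observes participants for a further six months and contacts them twice in that time.

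This matters because of the protocol's own rationale. Women with body dissatisfaction are allocated, about 38 of them, to an approach that the authors link to depression, anxiety and eating disorders. Women already diagnosed with these conditions are excluded at entry, so a diagnosis made during the trial would be new. The outcome scales are not designed to record it. A final report of few adverse events could then mean either that few occurred or that nobody asked, and a reader could not tell which.

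**Working it through.** **Adverse-event contacts and outcome contacts compared**

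| Period | Adverse-event enquiry described | Outcome data described |
|---|---|---|
| Weeks 0 to 8 (meetings) | Weekly, by conversation at meetings | Scales before the first meeting and after the eighth |
| After the last meeting to 3 months | None | Scales at 3 months |
| 3 to 6 months | None | Scales at 6 months |
| Women who stop attending | None once they stop | Not kept for follow-up below 6 of 8 meetings; data excluded if they discontinue or deviate |

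**What the scales can show.** The BSQ measures concern about body shape. The TFEQ-R21 measures cognitive restriction, uncontrolled eating and emotional eating, and higher scores mean more dysfunctional behaviour. The SCS measures self-compassion. Worsening on the first two would be visible at 3 and 6 months in women who stay. None of the three records a diagnosis, a treatment started, or any other health event.

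**Share of the timeline without enquiry.** The plan gives no figure for this. Inputs:
- Meetings: 8 weeks (Recruitment).
- Follow-up: 6 months after the last meeting (Recruitment), taken as 26 weeks. The conversion is an assumption.

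Total = 8 + 26 = 34 weeks.
With enquiry: 8 / 34 = 0.235, about 24%.
Without enquiry: 26 / 34 = 0.765, about 76%.

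**Illustration in events.** The documents give no adverse-event rate. Assume a constant hazard over 34 weeks and a cumulative risk r of 5%, 10% or 20%, in one arm of 38 (Sample size section). The risk by week 8 is 1 − (1 − r)^(8/34).

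| r | Risk by week 8 | Expected first events in 38 | Of these, after week 8 | Share after week 8 |
|---|---|---|---|---|
| 5% | 0.012 | 38 × 0.05 = 1.9 | 38 × (0.05 − 0.0120) = 1.4 | 76% |
| 10% | 0.024 | 38 × 0.10 = 3.8 | 38 × (0.10 − 0.0245) = 2.9 | 76% |
| 20% | 0.051 | 38 × 0.20 = 7.6 | 38 × (0.20 − 0.0511) = 5.7 | 74% |

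These are not predictions. They show only that, if harm were spread evenly over time, about three quarters of first events would fall where no enquiry is described.

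**Effect on sample size.** None. The 76 participants rest on body dissatisfaction and self-compassion, so added adverse-event items leave that number unchanged.

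**The case against.** The strongest objection is that this rests on the silence of a condensed article. A fuller protocol may hold a safety section, an ethics committee approved the study and receives periodic reports, and nothing says that events in follow-up would be ignored. Part of this stands: the finding is about what is described, and a fuller document could settle it. But the article does not merely omit the subject. It states frequency, place and method, and all three belong to the meetings. Followed as written, the rule ends at week 8.

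A second objection is that 76% is a share of calendar time, not of harm missed. That is correct. Monitoring is weekly throughout the active intervention, and no event rate is given. A woman who misses one meeting can also report at the next, so an occasional absence is not counted as a gap here.

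A reader might infer four stronger points that the document does not support:

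- **That harms in follow-up go undetected.** Worsening body dissatisfaction and eating behaviour are primary outcomes and are measured at 3 and 6 months in women who remain. Care and compensation are also offered to women who come forward. What is not systematically recorded is clinical events.
- **That monitoring closes before the expected harms appear.** The Discussion speaks of the long term without tying it to any number of weeks, and the Introduction gives no timing for depression, anxiety or eating disorders.
- **That the data of women who leave are deleted.** The text speaks of exclusion.
- **That the arms are questioned differently because the diet group has an individual online consultation in week 5.** That session replaces a group meeting and is held to review the diet. Nothing says that adverse events are asked about differently there.

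**Conclusion.** The point holds as a gap in safety data collection. As described, adverse events are sought only at the weekly meetings. Clinical events over about 26 of 34 weeks (76%), and harms in women who stop attending, are therefore not systematically recorded. Read literally, the exclusion of all data from women who discontinue or deviate would also remove from the results any event they had already reported.

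This rests on two assumptions: that six months is about 26 weeks, and that no fuller safety plan adds enquiry at the later contacts. The size of any resulting under-count is unknown, because the documents give no event rate. The gap does not affect the sample size or the primary comparison. It is worth correcting because the protocol itself names the clinical harms of concern and already contacts participants at the times when it could ask.

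**What to change.** Add one short adverse-event block, identical in both arms, to the existing Google Forms at week 8, 3 months and 6 months. Ask about:

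- any new health problem since the last form;
- any new diagnosis of, or treatment for, an eating, mood or anxiety disorder since the last form.

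Send the block also to women who stopped attending, unless they withdrew consent. State under Data management that these safety data are not subject to the exclusion rule for women who discontinue or deviate. Report the counts by arm, with the number of women who answered at each time. Keep the weekly conversation and the referral route as they are.

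The cost is a few more items on forms already in use, sending them to women who have left, and a researcher's time to read the replies. The change should be notified to the ethics committee under the protocol's own rule on amendments. If a fuller safety plan already covers follow-up, one sentence in Ethical aspects saying so would be enough for that part.

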Diet group: in the diet group, participants will complete a 24-hour food recall (24HR). They will receive a food plan calculated by a nutritionist using the Estimated Energy Requirement calculation [34] as a reference and adjusted to their routine based on the 24HR. The necessary nutritional adjustments will be made to ensure adequate fiber, macro, and micronutrient intake according to the Dietary Reference Intakes [35] for women. The total energy value will depend on the participant’s goal, with a calorie deficit of 300 kcal for those wishing to lose weight and a surplus of between 300–500 kcal for those wishing to gain weight. The macronutrient distribution will be the AMDR of 45–65% carbohydrates, 10–35% proteins, and 20–35% lipids. Table 2 shows the topics covered at each meeting. In the fifth week of the study, the participants will have an individual online consultation to re-evaluate the proposed diet and adjust it if necessary instead of a group meeting.

**Table 2 pone.0324030.t002:** Description of meetings in the Diet group.

Meeting	Central theme	Dynamics
Meeting 1: Presentation and performance of anthropometric measurements	Presentation and measurement of anthropometric measurements (weight and height) Application of anamnesis to calculate the diet plan	Conversation about the purpose of the group and the participants
Meeting 2: Motivation for weight loss	Consequences of being overweight and sedentary and the importance of cultivating healthy lifestyle habits	Written reflection
Meeting 3: How to choose food?	Classification of foods according to the Food Guide for the Brazilian population (2014)	Food classification dynamics
Meeting 4: How to read food labels?	Reading food labels	“Which food is healthier” dynamic
Meeting 5: Guidance and monitoring of the diet plan	Food plan	Individual guidance on the diet plan (online)
Meeting 6: Myths and truths about healthy eating	Demystifying beliefs about healthy eating	Dynamics of myths and truths
Meeting 7: How to use carbohydrates to my advantage	Glycemic index and glycemic load Smart food combinations	High-fiber foods vs. low-fiber foods
Meeting 8: Cultivating healthy habits in my life	Ways to cultivate healthy habits in the long term	Clarification of doubts Closing

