### Adherence, modifications, and concomitant care

In both groups, the importance of attendance and commitment to the meetings will be discussed. It will also be emphasized that it will be a safe space for listening, welcoming, and confidentiality. Participants will be asked about their feelings and doubts about their study process. The meetings will always occur on the same predetermined day, time, and location. Participants will be notified via smartphone before each meeting as a reminder. To increase adherence and commitment to the study, participants will also be offered activities to practice at home, such as food records, observation, and reflection exercises, or they will be asked to bring materials related to the next meeting (e.g., food packaging).

Adherence to the proposed interventions will be checked at each meeting. However, the difficulty of carrying out what is proposed does not compromise remaining in the group meetings.

Participants cannot change the group they have been allocated to. However, they are free to leave the study as they wish. The meeting protocol for both groups cannot be modified, as this could bias the study.

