### Randomization, allocation and masking of groups

Participants will be randomized to the Self-Compassion or Diet group with 1:1 allocation in the Random Group Generator (https://pt.rakko.tools/tools/59/). The nutritionists responsible for applying the interventions will have no contact with the randomization and will not know in advance who will go to which group, only the research coordinator.

Due to the nature of the intervention, it is not possible to blind the researchers and participants during the study’s conduction after the randomization process. However, the intervention and control groups will not interact in any way. Likewise, the statistical analysis will be blinded to the evaluator.

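### Adverse events are ascertained, as stated, only by conversation at unblinded, arm-specific meetings, so safety contact depends on attendance and harms described by arm are open to detection bias of unknown size and direction

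*Protocol article*

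**What the plan says.** Under Ethical aspects, adverse events are monitored weekly by researchers "in each meeting through conversations with the participants", with referral to the sponsor institution's health service according to the type of event. The article describes no other way of finding harms during the eight weeks.

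The setting of those conversations is described elsewhere in the article:

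- **Separation.** Under Randomization, allocation and masking of groups, "the intervention and control groups will not interact in any way".
- **Blinding.** The same section says "it is not possible to blind the researchers and participants during the study’s conduction after the randomization process". The only blinding it claims is that "the statistical analysis will be blinded to the evaluator".
- **Content.** Table 1 (self-compassion) covers self-criticism, personal history with food and the body, and mindful eating. Table 2 (diet) covers mainly food classification, labels, healthy-eating myths and carbohydrates, with a written reflection in Meeting 2.
- **Format.** In week 5 of the diet arm, "the participants will have an individual online consultation to re-evaluate the proposed diet and adjust it if necessary instead of a group meeting". Table 1 shows no matching individual contact.
- **Attendance.** Under Recruitment, "The adherence rate will be controlled, requiring a minimum participation of 75% (6 meetings" of the eight).
- **Contact outside meetings.** Under Data management, "the messages sent will be the same for both groups and will include reminders about the meeting days" and other practical details. Harm questions are not mentioned.
- **Women who leave.** Data management also requires that all data be excluded for those who discontinue or deviate from the intervention.
- **Common ground.** Under Adherence, modifications, and concomitant care, for both groups: "Participants will be asked about their feelings and doubts about their study process".

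**The concern.** The channel for finding harms is the intervention itself. What a woman mentions may depend on what her meeting is about, on whether she is speaking one-to-one, and on an asker who knows her allocation. If these influences differ between arms, reported harms will partly reflect how the meetings run and not only what happened to the women.

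The second issue needs no comparison between arms. A woman who stops coming is no longer asked, and the article gives no other way to reach her about harm. If her data are then removed under the exclusion rule, an event she had already reported could also disappear from the account.

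This matters in this trial because the Introduction names binge eating, guilt, anxiety, depression and eating disorders as possible consequences of energy-restricted dieting, and one arm receives a diet plan. Readers are likely to look at harms by arm even if no test is made. The point is confined to the eight weeks of meetings.

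**Working it through.** **Figures in the plan.** The article gives no harm rate and no detection probability. The one relevant figure is the attendance threshold, which reproduces: 6/8 = 75%.

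**Step 1: dependence on attendance.** With one check per meeting:

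- A retained woman may miss (8 − 6)/8 = 2/8 = 25% of checks. She can still report the event at her next meeting, so 25% is a share of checks and not of events lost.
- A woman who stops after Meeting 3 (a chosen example, not a documented pattern) is unasked for (8 − 3)/8 = 5/8 = 62.5% of the weeks. She has no next meeting, and no other route is stated.

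**Step 2: are the conditions of asking the same in both arms?**

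| Feature | Self-compassion | Diet |
|---|---|---|
| Nominal frequency | Weekly | Weekly |
| Channel | Conversation at meeting | Conversation at meeting |
| Asked about feelings and doubts | Yes | Yes |
| Asker knows allocation | Yes | Yes |
| Meeting content | Mainly reflective (Table 1) | Mainly educational (Table 2) |
| Week 5 format | Meeting on mindful eating | Individual online consultation |

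The first four rows match. The last two differ, and they may pull in opposite directions: reflective content could raise disclosure in the self-compassion arm, while a private consultation could raise it in the diet arm. The table therefore supports a risk of unequal detection and gives no direction.

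**Step 3: what unequal detection would do.** Let p be the true rate, equal in both arms, and s1 and s2 the detection probabilities. Then:

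observed rate = p × s, and observed ratio = (p × s1)/(p × s2) = s1/s2.

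All values below are assumptions, with p = 20%:

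| s1 | s2 | Observed rates | False difference | False ratio |
|---|---|---|---|---|
| 0.80 | 0.80 | 16% and 16% | 0 points | 1.0 |
| 0.90 | 0.75 | 18% and 15% | 3 points | 1.2 |
| 0.90 | 0.60 | 18% and 12% | 6 points | 1.5 |
| 0.90 | 0.30 | 18% and 6% | 12 points | 3.0 |

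Either arm could be the one with s1. The false ratio depends only on s1/s2, so the result runs from no bias to a large one according to inputs that the article does not supply. With 38 women per arm, the 6-point row corresponds to 0.06 × 38 = 2.3 women.

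**The case against.** The strongest reply is that monitoring sits under Ethical aspects and serves referral and care. Adverse events are neither a primary nor a secondary outcome, and Statistical analysis states no test of harms between arms. Frequency and channel are nominally equal, and both groups are asked about feelings and doubts. Some of the relevant distress is also measured identically outside meetings: the TFEQ-R21 covers uncontrolled and emotional eating and the BSQ covers body concern, both by Google Forms at baseline, week 8, 3 and 6 months. An article may also leave an adverse event form to the full protocol.

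Much of this stands, and it rules out several stronger readings that a reader might infer:

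- *Detection differs by arm.* The article shows conditions that could cause this, not that it happens.
- *Harms cannot be compared.* No comparison is planned, and the bias could be zero. The most that can be said is that a comparison would be unreliable.
- *The conversations are unstructured or held in front of the group.* The text says neither.
- *A missed meeting is a missed event.* For a woman who returns, the report may only be late.

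The reply does not remove the core. A question about feelings and doubts is not a harm question, and it is not described as reaching anyone outside the meetings. The scales do not measure low mood and are not collected between baseline and week 8. A fixed form in the full protocol could standardise the questions, but used within the stated channel it would still reach only women who attend.

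**Conclusion.** The point holds in conditional form. As stated, harm ascertainment is unblinded, takes place inside arm-specific meetings that differ in content and in week 5 format, and depends on attendance. A retained woman may go unasked at up to 25% of checks, probably with delay rather than loss. For a woman who stops attending, no stated route remains, and safety contact is lost.

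Any description of harms by arm is open to detection bias. Its size and direction cannot be computed from the article; the ratios from 1.0 to 3.0 rest wholly on assumed detection probabilities and must not be read as estimates.

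The conclusion assumes that the full protocol, which is not shown, adds no separate route to absent women. It affects neither the sample size nor the primary analysis. It is a worthwhile, inexpensive improvement and not a flaw that undermines the trial's efficacy question.

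**What to change.** Add one short harm question set, identical in both arms and answered privately, as a Google Forms link in the weekly WhatsApp message that already goes to both groups. Send it to every randomised woman who has not withdrawn consent, including those who missed a meeting and those who stopped attending. In addition:

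- Have the researchers who already monitor adverse events weekly review the answers, and say so in the protocol. Use the existing referral route under Ethical aspects unchanged.
- Keep the meeting conversations as a supplement, and record events found that way separately.
- State under Data management that the exclusion of data from women who discontinue or deviate does not apply to adverse event data. Otherwise the new answers could be discarded for the women the form is meant to reach.
- Notify the Ethics Committee, as the article requires for changes to tools.
- Record the date of the change, so that harms before and after it can be reported separately. The planned recruitment window opened on March 4, 2024, so some women may already have been followed under the present method.

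**Cost.** A small weekly burden for participants and for the researchers who review answers, more minor events reported in both arms, and different ascertainment for women enrolled before the change. The form and the message use channels the trial already runs. The interventions, sample size and primary analysis do not change.
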